**Secondary outcomes**

Rates of insertion and complications, the bleeding patterns and compliance during the first six months following IUC insertion.

***Eligibility criteria***

*Inclusion criteria:*

Women with an age above 18 years, general good health and good understanding of Swedish language, gestational length up to 63 days (determined with ultrasonography), who have given their informed consent will be eligible for study recruitment.

*Exclusion criteria:*

Women who do not wish to participate, women who are unable to communicate in Swedish and minors (i.e. women < 18 years of age) will not be enrolled for the study. Women with pathological pregnancies or abnormality of the uterus will be excluded from the study.

***Trial process and data collection***

The study protocol is designed according to the recommendations in the CONSORT statement. The study is a prospective randomised study. The study flow is planned as follows:

**Enrolment**

All women with a pregnancy up to 63 days gestation requesting termination of pregnancy by medical method and opting for post abortion IUC will be invited to be included in the study at the initial outpatient consultation. The women will receive detailed information regarding the study, as well as an informed consent form.

**Allocation and treatment**

Designated study nurses and doctors will be responsible for recruiting and examining study participants at the outpatient clinic. Eligible women with a pregnancy up to 63 days gestation who elect to participate in the study and who sign an informed consent form will be randomised into either :

Group 1 (early IUC insertion on day 5-9 after mifepristone)

or

Group 2 (outpatient standard follow-up and IUC insertion at 3-4 weeks after mifepristone) .

Study participants will be administered mifepristone and misoprostol according to routine. All women will be screened for bacterial vaginosis and Chlamydia infection, and treated if positive but not excluded from participation. Women will receive mifepristone (Mifegyne®, Exelgyn, Paris, France) 200 mg orally at the clinic. The day when mifepristone is administered counts as Day one. Thirty-six to 48 hours later women self administered 800 mcg misoprostol vaginally (Four tbl Cytotec® 200 mcg, Pfizer, New York, USA).

An ultrasound examination will be performed prior to insertion of the IUC, and the anterior-posterior thickness of the endometrium recorded as well as the presence of any remaining products of conception. Women diagnosed with a continuing pregnancy or a missed miscarriage, or with any surgical intervention or untreated genital infection after the abortion treatment will excluded from the trial.

Intensity of pain will be recorded on the visual analogue scale (VAS) ranging from zero to ten (worst possible pain) directly after IUC insertion before any use of analgesia.

Serum hemoglobin (S-Hb) and serum human chorion gonadotropin (S-hCG) will be determined on treatment day one (the day of mifepristone administration), on the day of IUC insertion, and at four weeks follow up.

The patients will be scheduled to return for a follow-up visit four weeks after the IUC insertion. Any complications such as genital infection, and expulsion will be recorded.

Women will be advised to keep daily records (starting on day one) on the bleeding pattern and notes of any adverse events as well as any concomitant medication. Intensity of bleeding will be reported in relation to the individual woman's normal menstrual bleeding on a scale from sparse (much less than menstrual bleeding) to heavy (much heavier than menstrual bleeding).

Women will be contacted by telephone at 3 and 6 months after the IUC insertion and asked to answer a questionnaire about pregnancy, expulsion, bleeding patterns, pelvic pain, pelvic infections, continuous use and overall satisfaction with the contraceptive method.

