**Randomization procedure**

Women who volunteer to participate in the study will be assigned, within each stratum (Cu-IUD or LNG-IUS), to either group at a ratio of 1:1 using a computer generated randomization list. The randomisation procedure is a third party concealed randomisation. A study nurse, not directly involved in the study, will perform block randomisation, 10 subjects to each block, and create opaque, numbered, envelopes containing the randomisation group for each participant. Randomisation will occur upon opening the envelope consecutively after the participant has signed informed consent to participate.

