**Registration and reporting of suspected adverse events**

Complications and the number of women requiring surgical intervention (e.g. for on-going pregnancy, retained products of conception, ectopic pregnancy) will be recorded.

Any unexpected and serious side effects and suspected adverse reactions will be immediately reported to the project leader as well as the trial steering committee. The regional ethics committee will also be notified according to local regulations.

Any unexpected adverse event that occurs during the study will be reported to Läkemedelsverket according to LVFS 2003:6 (electronically). This will also be recorded in the patient file which will be kept (with the other study documents) for at least ten years.

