***Statistical analysis; power calculations - sample size***

***Sample size***

The main outcome of the study is to detect any difference in expulsion rate between women assigned to the early and the delayed IUC insertion groups. Since no data on expulsion rates of IUC after early post medical insertion is available at the time of the study start we assumed that expulsion rate after early insertion post medical abortion is similar to the expulsion rate after immediate insertion post surgical abortion. In a previous study of immediate IUC insertion post surgical abortion, the expulsion rate during the first year was found to be 15,4 % in the immediate group compared to 2,8% in the delayed insertion group (6). With 60 patients in each randomized group we will have a power of 78% in a one-sided test (alpha-level: 5%) to detect a difference between the groups of the same magnitude as in the study by Gillett et al. To evaluate the differences between the groups regarding independent nominal data such as expulsion, side-effects and compliance, the chi squared test will be used. Continuous variables with a normal distribution, such as age will presented as medians (range) and compared using Mann-Whitney U-test. Also discrete numerical variables such as parity and bleeding patterns will be presented as medians (range) and assessed for normality and comparison using the Mann-Whitney U-test. Results will be considered statistically significant if P-value < 0·05.

The data will be analysed using the intention-to-treat principle, including all women in the groups as randomized. Numbers and proportions of women receiving IUC insertion will be calculated by intervention. Both interventions will be compared using both absolute and relative measures with 95% confidence intervals.

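### Women are excluded from the trial for events after randomisation, which contradicts the intention-to-treat statement, removes women whose events are outcomes, and may act over different time windows in the two arms

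*Protocol*

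**What the plan says.** Recruitment takes place before the abortion: under Enrolment, women "will be invited to be included in the study at the initial outpatient consultation". Under Randomization procedure, "Randomisation will occur upon opening the envelope consecutively after the participant has signed informed consent to participate". Allocation and treatment describes those randomised as "Eligible women with a pregnancy up to 63 days gestation who elect to participate in the study and who sign an informed consent form", so they are still pregnant at allocation.

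The same section then states that "An ultrasound examination will be performed prior to insertion of the IUC". Shortly afterwards comes the exclusion. It opens with "Women diagnosed with a continuing pregnancy or a missed miscarriage" and extends to women "with any surgical intervention or untreated genital infection after the abortion treatment will excluded from the trial". There are thus four grounds, and the consequence is removal from the trial, not merely from insertion.

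Two other places bear on these women. Sample size says: "The data will be analysed using the intention-to-treat principle, including all women in the groups as randomized". Registration and reporting of suspected adverse events says: "Complications and the number of women requiring surgical intervention (e.g. for on-going pregnancy, retained products of conception, ectopic pregnancy) will be recorded". Secondary outcomes lists insertion rates and complications. Interventions sets insertion at 5 to 9 days after mifepristone in Group 1 and at 3-4 weeks in Group 2, and times all follow-up from insertion.

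**The concern.** A woman cannot be both removed from the trial and analysed as randomised. The protocol has one sentence for each and nothing that reconciles them. An SAP could define the analysis set, but it could not recover outcomes for women whom the protocol had stopped following.

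The grounds for removal are also not neutral. A woman who has a surgical intervention or a continuing pregnancy is a complication, and if she gets no IUC she is a non-insertion. Removing her deletes the event from the numerator and the woman from the denominator of the outcomes meant to describe such cases.

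Finally, the pre-insertion examination falls at different times by design. A rule applied at that examination selects women over a period set by their allocation, so the women who remain need not be comparable between the arms.

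**Working it through.** **1. Order of events.** Consent at the initial consultation (Enrolment), then the envelope (Randomization procedure), then mifepristone, then misoprostol, then the pre-insertion ultrasound (Allocation and treatment). All four exclusion grounds are conditions after the abortion treatment, so every exclusion under this rule comes after randomisation.

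**2. The statements side by side.**

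| Place in the protocol | Woman with a surgical intervention before insertion |
|---|---|
| Allocation and treatment | Removed from the trial |
| Sample size | Analysed in her randomised group |
| Registration and reporting | Her intervention is recorded |
| Secondary outcomes | Relevant to insertion rate and to complications |
| Interventions; telephone contacts | No scheduled contact, since follow-up is timed from an insertion she did not have |

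The first row cannot be followed together with the second.

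**3. Length of the window, if it closes at the pre-insertion examination.** Early arm: 5-9 days. Delayed arm: 3-4 weeks = 21-28 days.
- Difference: 21 − 9 = 12 days to 28 − 5 = 23 days.
- Ratio: 21/9 = 2.3 to 28/5 = 5.6.

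The closing point is inferred from the placement of the sentence after the ultrasound; the protocol does not state it.

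**4. Insertion rate.** The protocol gives no exclusion rate, so 5-15% per arm is an assumption for illustration. Suppose k of 60 women are excluded and all others get an IUC. With exclusion the rate is (60 − k)/(60 − k) = 100%; as randomised it is (60 − k)/60.
- k = 3 (5%): 57/60 = 95%.
- k = 6 (10%): 54/60 = 90%.
- k = 9 (15%): 51/60 = 85%.

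Exclusion hides exactly the fraction excluded. If that were 5% in one arm and 15% in the other, a 10-point difference (95% − 85%) would disappear.

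**5. Power.** Inputs from Sample size: 60 per group, 15.4% v 2.8%, one-sided 5%. Pooled-variance normal approximation: power = Φ[(d − 1.645 × SE0)/SE1].
- d = 0.154 − 0.028 = 0.126; mean proportion = 0.091.
- SE0 = √(2 × 0.091 × 0.909/60) = 0.0525.
- SE1 = √[(0.154 × 0.846 + 0.028 × 0.972)/60] = 0.0512.
- Power = Φ(0.773) = 78.0%. The stated 78% reproduces.

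No allowance for exclusions is stated. Under assumed exclusions, with the same formula (for unequal groups, the mean proportion weighted by size):

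| Excluded, early / delayed | n | Power |
|---|---|---|
| 0% / 0% | 60 / 60 | 78.0% |
| 5% / 5% | 57 / 57 | 76.2% |
| 5% / 10% | 57 / 54 | 74.9% |
| 10% / 10% | 54 / 54 | 74.1% |
| 5% / 15% | 57 / 51 | 73.4% |

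The loss runs from 78.0 − 76.2 = 1.8 to 78.0 − 73.4 = 4.6 points.

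**6. Expulsion rate.** Planned expulsions: 60 × 0.154 = 9.2 early and 60 × 0.028 = 1.7 delayed. Removing delayed-arm women who have no IUC, and hence no expulsion, changes only the denominator: 1.68/60 = 2.8%, 1.68/58 = 2.9%, 1.68/55 = 3.1%. The effect is small unless the removed women would have been unusually likely to expel an IUC, and nothing in the protocol speaks to that.

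**The case against.** The core contradiction has no answer in the text, but several stronger readings that a reader might draw do not hold.

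- *Only the delayed arm loses women.* The rule is the same for both arms, and an early-arm woman with a qualifying condition by day 5-9 is removed too. The document supports unequal exposure to the rule, no more.
- *The bias runs against early insertion.* The delayed arm has longer for interventions to accrue, but an ultrasound at 5-9 days may find conditions not yet resolved and so remove more early-arm women. The direction is open.
- *Any infection between the two insertion times removes a delayed-arm woman.* Only untreated infection excludes. An infection treated before the 3-4 week visit does not, on the wording.
- *The window certainly closes at insertion.* This is inferred. If the rule also runs after insertion, the asymmetry weakens, but the rule then removes post-insertion interventions as well and the conflict with the safety section grows.
- *Intention-to-treat analysis is impossible.* That goes too far. The safety section records surgical interventions without limiting this to retained women, and Sample size plans insertion proportions by group. Once the wording is reconciled, the analysis can be done.

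One objection stands and widens the remedy. Secondary outcomes can be read as counting complications only after IUC insertion. On that reading an event on day 15 in the delayed arm precedes the outcome window even if nobody is excluded, so deleting the exclusion alone would not make the arms comparable.

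**Conclusion.** The protocol is wrong as written: exclusion after randomisation and analysis of all women as randomised cannot both be carried out, and the excluded events are themselves outcomes. This rests on the text alone.

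Possible dependence of exclusion on allocation rests on one inference, that the rule is applied at the pre-insertion examination. Given that, the window is 12 to 23 days longer in the delayed arm. The direction and size of any resulting bias cannot be determined from the protocol. The impact is most direct on insertion rates and complications. A material effect on the expulsion rate is not shown, and the cost in power is modest: about 2 to 5 points under assumed exclusions of 5-15% per arm. The sample size figure itself is correct on its own inputs.

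**What to change.** Reconcile Allocation and treatment, Registration and reporting of suspected adverse events, and Sample size:

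- Replace the removal from the trial with a statement that, whatever is decided clinically about insertion, every randomised woman stays in follow-up and is analysed in her randomised group. The clinical decision itself is not touched.
- Where no IUC is placed, count her as not inserted, and count her surgical intervention or infection as a complication.
- Count complications from one origin in both arms, the day of mifepristone or of randomisation. This also gives women without an IUC a follow-up schedule.
- Report non-insertion with reasons, by arm.
- State how women without an IUC enter the expulsion analysis, since the primary outcome is timed from insertion and they have no such origin.

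A sensitivity set that excludes only events up to day 9 may look like a way to equalise the arms, but it would not do so. Early insertion can occur from day 5, so a day-8 event may fall after insertion in that arm, and no delayed-arm examination is scheduled by day 9 to find the same conditions.

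The cost is revised wording and a few extra follow-up calls. Complication and non-insertion counts may rise.

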**Outcomes and adverse events**

Partial expulsion will be defined as the presence of the IUC within the cervical canal, and complete expulsion as the passage of the IUC out of the cervix entirely. Pelvic infection will be considered to be present in women with purulent discharge, cervical or uterine tenderness, or a tender adnexal mass, with or without fever or leukocytosis.

**Randomization procedure**

Women who volunteer to participate in the study will be assigned, within each stratum (Cu-IUD or LNG-IUS), to either group at a ratio of 1:1 using a computer generated randomization list. The randomisation procedure is a third party concealed randomisation. A study nurse, not directly involved in the study, will perform block randomisation, 10 subjects to each block, and create opaque, numbered, envelopes containing the randomisation group for each participant. Randomisation will occur upon opening the envelope consecutively after the participant has signed informed consent to participate.

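### Randomisation is stratified by device, but the named chi-squared and Mann-Whitney tests ignore the stratum: negligible for expulsion, a possible loss of power for bleeding

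*Protocol*

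**What the plan says.** Under Randomization procedure, women are "assigned, within each stratum (Cu-IUD or LNG-IUS), to either group at a ratio of 1:1", and a study nurse "will perform block randomisation, 10 subjects to each block". Device type is therefore a true stratification factor, and the arms are held close to equal within each device.

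The tests are named under Sample size. For comparisons "regarding independent nominal data such as expulsion, side-effects and compliance, the chi squared test will be used". For bleeding, "discrete numerical variables such as parity and bleeding patterns will be presented as medians (range") and "assessed for normality and comparison using the Mann-Whitney U-test". The section mentions no stratified test, no adjustment for device and no summary by device. The power statement is also an unstratified comparison of two proportions.

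The Objectives put both devices into one comparison of early with delayed insertion. Expulsion at 6 months is the primary outcome, and bleeding pattern is a secondary outcome.

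**The concern.** Blocking within device keeps device differences almost entirely out of the between-arm contrast. A test that ignores device still counts the variation between devices as random noise. When device predicts the outcome, the assumed variance is then larger than the true variance of the contrast. The test rejects too rarely under the null and has less power under the alternative.

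Bleeding is the outcome to watch. A copper device and a hormone-releasing device share one median and one rank test, and if their bleeding differs, the pooled median may describe neither group. What is at stake is efficiency that the design has already paid for, mainly on a secondary outcome.

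**Working it through.** **1. The plan's own figure.** Inputs from Sample size: "15,4 % in the immediate group compared to 2,8% in the delayed insertion group", 60 per group, one-sided 5%. With the pooled proportion (0.154 + 0.028)/2 = 0.091:

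- SE under the null = √(2 × 0.091 × 0.909/60) = 0.0525
- SE under the alternative = √[(0.154 × 0.846 + 0.028 × 0.972)/60] = 0.0512
- Power = Φ[(0.126 − 1.645 × 0.0525)/0.0512] = Φ(0.773) = 78.0%

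The stated 78% reproduces as an unstratified calculation. The simulated chi-squared powers below start near 83% because they use actual binomial counts and not this normal approximation. Exact enumeration of the uncorrected one-sided test gives 82.8%.

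**2. Expulsion.** Assumptions: 30 women per device in each arm, overall rates kept at 15.4% and 2.8%, device rates differing by a stated factor in both arms; 400,000 simulated trials per row.

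| Device ratio | One-sided power, chi-squared / CMH | Two-sided power, chi-squared / CMH |
|---|---|---|
| 1 | 82.9% / 82.9% | 71.9% / 72.2% |
| 2 | 83.0% / 83.0% | 72.0% / 72.8% |
| 3 | 83.1% / 83.3% | 72.3% / 73.8% |

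Two-sided size at ratio 3 is 4.8% for chi-squared and 5.2% for CMH (Cochran-Mantel-Haenszel), so part of the 1.5-point gap reflects CMH running slightly above 5%.

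Interval width for the risk difference can be checked by hand. At ratio 3 the device rates are 23.1% and 7.7% early, 4.2% and 1.4% delayed.

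- Stratified variance = (0.231 × 0.769 + 0.077 × 0.923 + 0.042 × 0.958 + 0.014 × 0.986)/120 = 0.002523
- Unstratified variance = 0.1575/60 = 0.002625
- Width ratio = √(0.002625/0.002523) = 1.02, so about 2% wider

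**3. Bleeding.** Assumptions: normal outcome, arm effect 0.5 SD, 60 per arm, two-sided 5%, device shift D in within-device SD; 20,000 simulated trials per scenario. Size ranges for the 30/30 mix cover the separate simulation runs.

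| D (SD) | Size, Mann-Whitney, 30/30 mix | Power, Mann-Whitney, 30/30 mix | Size, Mann-Whitney, 15/45 mix | Power, Mann-Whitney, 15/45 mix |
|---|---|---|---|---|
| 0 | about 5% | 75% | 5.0% | 76% |
| 0.5 | 4.4% | 74% | 4.4% | 74% |
| 1 | 2.6–3.1% | 67% | 3.3% | 70% |
| 1.5 | 1.1–1.4% | 56% | 2.1% | 62% |

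The van Elteren test (rank-sum stratified by device) has size about 5% and power about 75% in every row and both mixes.

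**4. Hand check of the sizes.** If a share w of each arm uses one device, the variance that the unstratified test assumes is inflated by 1 + w(1 − w)D², so the effective critical value is 1.96 × √[1 + w(1 − w)D²].

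- w = 0.5, D = 1: 1.96 × √1.25 = 2.19, size 2.8%
- w = 0.5, D = 1.5: 1.96 × √1.5625 = 2.45, size 1.4%
- w = 0.25, D = 1: 1.96 × √1.1875 = 2.14, size 3.3%

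This is the large-sample formula for a comparison of means, and it agrees with the simulated rank tests.

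**5. Ordered scale.** The protocol records bleeding intensity relative to the woman's own menstruation, from sparse to heavy. On an assumed five-level tied scale, with a 1 SD device shift and a 30/30 mix, size is 3.0% unstratified against 4.9% stratified, and power is 63% against 71%.

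**The case against.** - **The primary outcome is essentially untouched.** This stands. The trial is sized on expulsion with a one-sided test, and there the cost is at most about 0.2 points.
- **The bleeding figures rest on assumed shifts.** This also stands. The protocol does not say that bleeding differs by device, nor by how much. At 0 SD nothing is lost, and at 0.5 SD at most about 2 points of power.
- **A normal outcome is not the planned one.** Fair, but the five-level scale gives a loss of the same size (8 points at 1 SD), so the conclusion does not depend on normality. The figures remain illustrations and are not estimates for this trial.
- **A statistical analysis plan could add stratified tests.** True, but the protocol is not silent. It names the tests, and as named they leave out its own stratification factor.

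A reader might go further and infer that the trial's intervals are wrong. The documents do not support that. Intervals are too wide only if device is prognostic, and for expulsion the excess is about 1–3%. For bleeding the Sample size section names medians with range and no interval for a difference in medians.

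**Conclusion.** The mismatch is in the text: allocation is stratified by device and the named tests are not. The direction is certain if device is prognostic: conservative tests and less power. For expulsion the loss is negligible. For bleeding it runs from nothing at no device difference to about 8 points of power at 1 SD (67% against 75%) and about 19 points at 1.5 SD (56% against 75%) with an even device mix; with a 15/45 mix it is about 5 and 13 points. These sizes rest on the assumed shift, device mix and 0.5 SD arm effect, none of which the protocol gives.

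It would be wrong to conclude that the trial is invalid, that false positives are inflated, or that the sample size fails on this account. None of these follows. This is a worthwhile efficiency improvement, chiefly for a secondary outcome.

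**What to change.** In the Sample size section:

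- For expulsion, side-effects and compliance, replace the chi-squared test with the Cochran-Mantel-Haenszel test stratified by device. Report Mantel-Haenszel risk differences and risk ratios with 95% confidence intervals, which also supplies the absolute and relative measures the section already promises.
- For bleeding patterns, replace the Mann-Whitney test with the van Elteren test stratified by device, and show medians by device as well as overall.

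The cost is wording alone. Device is already recorded as the randomisation stratum, so no extra women, visits or data are needed. If device turns out not to matter, the simulations show practically no loss from stratifying (expulsion power 82.9% either way one-sided; bleeding about 75% either way).

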***Setting/Centres***

The Department of Obstetrics and Gynaecology, Karolinska University Hospital/ Karolinska Institutet, Stockholm, Sweden.

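### A single block size of 10, printed in the protocol of an unmasked single-centre trial, leaves up to about one allocation in six deducible by a recruiter who keeps a tally; varying and withholding the sizes would be a minor, low-cost improvement.

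*Protocol*

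**What the plan says.** The Randomization procedure section of the protocol allocates women "to either group at a ratio of 1:1 using a computer generated randomization list", separately for copper and hormonal devices. A nurse outside the trial team prepares the list by "block randomisation, 10 subjects to each block, and create opaque, numbered, envelopes". No other block size is mentioned, and nothing says that the size is kept from recruiting staff.

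The same section gives two safeguards: "The randomisation procedure is a third party concealed randomisation", and "Randomisation will occur upon opening the envelope consecutively after the participant has signed informed consent to participate". The Enrolment section adds a third: every woman who meets the criteria is to be invited at her first outpatient consultation.

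Setting/Centres names one site: "The Department of Obstetrics and Gynaecology, Karolinska University Hospital/ Karolinska Institutet, Stockholm, Sweden". Under Allocation and treatment, "Designated study nurses and doctors will be responsible for recruiting and examining study participants at the outpatient clinic". The arms are insertion on day 5 to 9 after mifepristone and insertion at 3 to 4 weeks. No masking is described.

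**The concern.** An opaque envelope hides the next allocation but not the earlier ones. Here the earlier ones are evident to clinic staff from the insertion date. The device type a woman chooses tells staff which stratum's list applies. If every block holds exactly five of each arm, and the protocol says so, the remaining places in a block can be counted down. Once one arm's five places are used, the rest of the block is known.

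What is at stake is selection before randomisation. A recruiter who knows or suspects the next allocation could encourage or discourage a particular woman, even without intending to. Intention-to-treat analysis does not repair that. Events are few: at the planning rates of 15.4% and 2.8% with 60 per group, expected expulsions are 60 × 0.154 = 9.2 and 60 × 0.028 = 1.7. The insertion rate, a secondary outcome, depends on who returns, and the Scientific background cites 42% non-return under delayed insertion after surgical abortion. Staff may therefore hold views about which women suit which arm.

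**Working it through.** **Inputs.** Block size 10, ratio 1:1 and two strata (Randomization procedure); 60 women per group, 120 in all (sample size section). The split of the 120 between the strata is not given, so all splits are considered.

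**The plan's own figure.** The protocol gives no predictability figure. Its one computed design figure is 78% power. With a pooled rate of (0.154 + 0.028)/2 = 0.091:

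- null standard error: √(2 × 0.091 × 0.909/60) = 0.0525
- alternative standard error: √((0.154 × 0.846 + 0.028 × 0.972)/60) = 0.0512
- power: Φ((0.126 − 1.645 × 0.0525)/0.0512) = 78.0% one-sided

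This reproduces the stated value and does not depend on the block size.

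**Certain allocations in one block of 10.** Position k is determined if one arm already has all five of its places among the first k − 1. The probability is 2 × C(k−1, 5)/C(10, 5), with C(10, 5) = 252.

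| Position | Calculation | Probability already determined |
|---|---|---|
| 1 to 5 | 0 | 0% |
| 6 | 2/252 | 0.8% |
| 7 | 12/252 | 4.8% |
| 8 | 42/252 | 16.7% |
| 9 | 112/252 | 44.4% |
| 10 | 252/252 | 100% |

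The sum is 420/252 = 1.667 per block, or 16.7%. The general form 2/(B + 2) gives 2/12 = 16.7%. Full enumeration of the 252 blocks agrees.

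**Over 120 women.** If both strata end on complete blocks: 12 × 1.667 = 20 (16.7%). In the least predictable split, such as 55 and 65, there are 11 complete blocks and two half-blocks with nothing determined: 11 × 1.667 = 18.3 (15.3%). The range over all splits is 18.3 to 20.

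**Best guess.** Always guessing the arm with more places left is right with probability (m + 2^(2m−1)/C(2m, m) − 0.5)/(2m). For m = 5 this is (5 + 512/252 − 0.5)/10 = 65.3%, against 50% by chance.

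**Randomly varied sizes.** These were simulated with 60 women per stratum and an observer who knows the set of sizes and every past allocation, but not the order of the sizes.

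| Design | Known with certainty | Predictable with at least 90% confidence | Average best guess |
|---|---|---|---|
| Fixed 10 (exact) | 16.7% | 16.7% | 65.3% |
| 8, 10, 12 mixed | about 1.3% | about 2.6% | 64.7% |
| 4, 6, 8 mixed | about 2.4% | about 5.0% | about 68% |

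Repeat runs of the 8/10/12 design gave 1.3% to 1.4% and 2.6% to 2.8%, which is simulation error. For 120 women, 1.3% is fewer than two.

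**The case against.** The strongest reply is that the remedy barely changes overall guessability. Under the Blackwell–Hodges guessing model, selection bias scales with correct guesses in excess of 50%. That excess falls only from 15.3 to 14.7 points, about 4% of it. This stands. A recruiter acting on hunches is hardly slowed; a recruiter acting on certainty is.

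The second reply is that the safeguards are real. Inviting all eligible women leaves no stated discretion over whom to approach. Consent before opening blocks changes once the allocation is seen. The 63-day gestation limit leaves little room to delay enrolment. These points also stand, as limits. None of them stops deduction from earlier allocations, or a difference in how warmly a woman is encouraged to join before she consents.

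Third, fixed blocks are a legitimate design, and 10 is less predictable than smaller fixed sizes: the determined share is 2/8 = 25% at 6 and 2/6 = 33% at 4. Of the 20 determined allocations, 12 are simply the last place in each block. This is fair and keeps the point minor.

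A reader might also infer that one small team recruits the women, follows them up and so sees every allocation. The protocol does not say this. It assigns recruiting and examining to designated nurses and doctors, gives no team size, and does not say who makes the follow-up calls.

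**Conclusion.** The point holds as a minor weakness in a rule that the protocol itself fixes. Between 15.3% and 16.7% of allocations (18.3 to 20 of 120 women, on average) could be known with certainty before opening.

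This rests on three assumptions: the recruiter knows the block size, as a reader of the protocol would; someone keeps a complete tally by stratum across all recruiters; and past allocations are visible. The last is inferred from the insertion timing and the absence of any described masking; the protocol does not call the trial open.

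A reader might conclude that concealment has failed, or that the expulsion or insertion-rate comparison is biased. The document does not support either. It shows that allocations are deducible, not that anyone would deduce them or act on it, and neither the direction nor the size of any bias can be derived from it. Nothing here is contradictory or miscalculated, and the 78% power figure is unaffected.

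**What to change.** Have the third-party nurse generate the list with randomly ordered block sizes within each device stratum, for example 8, 10 and 12. Avoid mixes of small blocks: 4, 6 and 8 would raise the average best-guess rate to about 68%, above that of the present design. In the protocol, say only that block sizes vary, and hold the sizes in a file that recruiting staff cannot see.

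The change should be presented for what it does: it removes nearly all certain knowledge and leaves the average guess rate of an observer who knows the size set almost where it was.

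The cost is one setting in the list generator, one protocol sentence and slightly more possible imbalance at the end of each stratum.
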